### Outcome measures

The proposed outcome measures for the definitive trial have been chosen to reflect both clinical and patient-centred factors. The main primary outcome measure will be change in quality of life as measured by the mini Asthma-related Quality of Life Questionnaire (mAQLQ) [35]. The proposed secondary outcomes will include measures of asthma control, healthcare resource use, patient self-efficacy and cost-effectiveness. Asthma control will be assessed from the scores on the Asthma Control Questionnaire (ACQ) [38] and data from the Health Services Resource Use (HSRU) questionnaire. Cost-effectiveness will be measured as a cost per Quality-Adjusted Life Year (QALY) of the intervention compared to the control group. Utilising the HSRU data, the costs of overall asthma-related healthcare resource use over the 6-month pre- and post-trial period from an NHS perspective will be calculated. QALYs over the 6-month trial period will be derived from EQ-5D-3L responses [43]. The GOAL-setting process will be assessed by recording the number and type of goals identified and achieved. This information will be gleaned from the patient-completed goal setting tool and their level of confidence for achieving their identified goals from their completed action plan.

For this pilot trial, the key outcome measures of interest are aimed at enabling us to assess the feasibility of and plans for conducting the definitive trial:

• Practice and patient recruitment rates

• Retention rates

• Likely cost of the intervention

• Acceptability of GOAL tool and action plan process to adults with asthma

• The variability of the main outcome measure

• The sample size required to effect change in asthma-related quality of life

• Acceptability, effectiveness and ease of use of the chosen measuring instruments

### Sample size calculation

As this is a feasibility study we have not undertaken a formal sample size calculation. A sample size of eight practices will allow for four practices in each health region. The aim will be to recruit approximately 80 patients in total (40 in each arm).

### Fidelity: practice and practice nurse

Commitment to the project process will be facilitated by the use of clear written information on what the study involves; support for recruitment by the SPCRN; use of individual patient case report forms to log each stage of the project process; guidance to practices on identifying eligible patients; a clear account of payment for practice time; and an extensive training workshop for participating nurses. The project researchers will be in regular contact with the practices to offer support, answer any questions and solve any problems.

### Withdrawal of patients from the study

There are five points at which consenting patients could withdraw from the study:

(1) prior to completing baseline questionnaires

(2) prior to attending the asthma review appointment with the practice nurse

(3) prior to the 6-week telephone follow-up

(4) prior to completing the 3-month follow-up questionnaires

(5) prior to completing the 6-month follow-up questionnaires

### Data management

The TCTU will be responsible for data management, data quality assurance, backup, business recovery and statistical analysis.

### Statistical analysis

Data analysis, using the following analysis plan, will be undertaken blind to the allocation arm. The primary analysis will be a per protocol analysis based on an intention to treat [44].

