### Trial procedures

Once a patient has consented to take part in the trial by returning the expression of interest form and signed consent, they will be telephoned by a researcher, at which time their eligibility to participate in the project will be confirmed and the baseline questionnaires completed. Patients will then be asked to contact their practice and arrange an appointment for an asthma review. The research team will liaise with the general practice to ensure all consenting patients who have completed baseline questionnaires have made an appointment. Patients will be seen by the PN in their usual clinic setting.

Patients in the intervention group practices will be sent the goal-setting tool prior to the review appointment with instructions to complete it independently at their convenience and to take it with them to the review appointment. Patients not bringing it to the review will be asked to complete it in the waiting area prior to the review.

The nurse in both study groups will conduct a review consultation in line with clinical guidelines [control assessment; peak expiratory flow (PEF); check of inhaler technique; review of medication, etc.] In addition the nurse in the intervention group will review the patient’s own goals as identified using the goal-setting tool. Nurse and patient will discuss the individual goals and, if necessary, the appropriateness of and the priority given to each goal. An individualised action plan will be discussed, negotiated and agreed upon, tailored to the number and complexity of the elicited goals. The written record of the personalised GOAL action plan will be given to the patient. This plan will be in addition to any symptom-related asthma action plan provided by the practice. Nurses in both the intervention as well as control groups will be asked to audio-record the review consultations using a digital recorder provided by the research team.

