Patients receiving the intervention will be contacted by the researcher, via the telephone, 6 weeks after their review consultation to elicit their perceived progress in implementing their plans and perceived efficacy of the plans in achieving associated goals. Follow-up outcome questionnaires will be completed at 3 months and again at 6 months post review for all patients. Patients will have the option of receiving these by post and completing it themselves, or to complete them via the telephone with a researcher. The former will be supported by a telephone reminder to patients where necessary.

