### Measures and measurement instruments

• Asthma-related quality of life: Assessed using the mAQLQ [35]. The mAQLQ measures the functional problems experienced by people with asthma. This is a validated and widely used tool in clinical trials [36,37] designed to ask adults with asthma about the physical, emotional occupational, and social problems most troublesome to them on a day-to-day basis. A clinically relevant improvement is an increase of ≥0.5 in individual mAQLQ mean scores. We will also compare mAQLQ scores at 3-months post-randomisation to establish the most appropriate time-point for assessment of clinical endpoints.

• Asthma Control Questionnaire (ACQ) [38]: The shortened version of the ACQ has six questions (the top scoring 5 symptoms and daily rescue bronchodilator use). Patients are asked to recall how their asthma has been during the previous week and to respond to the symptom and bronchodilator use questions on a 7-point scale (0 = no impairment, 6 = maximum impairment). The questions are equally weighted and the ACQ score is the mean of the six questions and therefore between 0 (totally controlled) and 6 (severely uncontrolled).

• Healthcare resource use (HSRU): This is a reflection of asthma control. Data will be collected from patient records using a form designed for use in previous studies [39,40]. Data will include the number and type of asthma-related consultations, number of exacerbations, emergency asthma medication use, etc., in the 6 months pre- and post-intervention.

• Perception of patient empowerment using the Patient Enablement Instrument [41]: This six-question (4 responses) tool measures a patient’s confidence, understanding and ability to cope with their health and illness.

• Quality of life using the EQ-5D-3 L [42]: Applicable to a wide range of conditions, this simple questionnaire is quick to complete. It measures health outcomes by classifying patients into one of 243 health states (5 dimensions, each with 3 levels). The five dimensions are mobility, self-care, usual activities, pain/discomfort and anxiety/depression. The data are translated into ‘utility scores’ using the UK population tariff (Dolan, 1995) and used to estimate Quality Adjusted Life Years in cost-effectiveness analysis.

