#### Comparison between treatment arms

The difference in the validated mAQLQ score between the intervention and control groups at baseline and 3 and 6 months post-intervention will be compared, adjusting for practice level stratum (region and list size). A clinically relevant improvement is an increase of ≥0.5 in individual mAQLQ mean scores [35]. Quality of life using the validated mAQLQ was measured at the baseline (January to May 2013) prior to the HCP asthma review appointment, and repeated at 3 months and 6 months post-intervention. Comparison of the mAQLQ scores at 3 months post-intervention as well as at 6 months post-intervention will enable us to establish the most appropriate time point for assessment of clinical endpoints. Changes from baseline to six months post intervention will be assessed in SPSS for Windows using multiple regression analysis with 6-month mAQLQ as outcome and baseline mAQLQ as covariate along with arm of trial (intervention/control) in the model. We will be adjusting all models for clustering within practices and matching by size. Transformations of the outcome variables will be used where necessary if these are not normally distributed. All analyses will be stratified by the stratification factors. We will estimate an ICC for all potential outcomes in the full trial. Consequently sample size estimates will be made for the full trial.

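### The primary analysis is named as both per protocol and intention to treat, and the sections disagree on the date from which follow-up is counted

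*Protocol article*

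**What the plan says.** The Statistical analysis section of the protocol article defines the primary analysis in one sentence: "The primary analysis will be a per protocol analysis based on an intention to treat [44"]. The same section promises that the analysis will be blind to arm. No section shown gives criteria for a per-protocol set or says how the two terms fit together.

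Three sections give the timing of the outcome questionnaires:

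- Trial procedures: "Follow-up outcome questionnaires will be completed at 3 months and again at 6 months post review for all patients".
- Comparison between treatment arms: the mAQLQ is "repeated at 3 months and 6 months post-intervention".
- Measures and measurement instruments: "We will also compare mAQLQ scores at 3-months post-randomisation to establish the most appropriate time-point".

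The route to the review matters here. Consent and the baseline questionnaires come first, and then "Patients will then be asked to contact their practice and arrange an appointment for an asthma review". The research team checks with the practice that an appointment has been made. The Withdrawal section lists, as one of five withdrawal points, leaving the study "prior to attending the asthma review appointment with the practice nurse".

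**The concern.** A per-protocol set is chosen by what happened after allocation, and an ITT set is not. If one sentence names both as primary, either could be reported as the planned analysis once the data are known.

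Although this is a feasibility trial, its results depend on the choice. The variability of the main outcome and the sample size for the full trial are listed as key outcomes. The analysis section takes the ICC and the full-trial sample size from these data. The Cost-effectiveness section bases the value-of-information analysis on the means, variances and covariance of the cost and QALY differences. If the population is not fixed, none of these inputs is fixed.

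The conflicting anchors are a second, smaller problem. ITT needs an outcome date for every patient, and a date counted from the review does not exist for someone who has none.

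**Working it through.** **Population.** The planned size is 8 practices × 10 patients = 80, or 40 per arm, which agrees with the stated target. It is a recruitment target with no alpha, power, SD or dropout behind it, so there is no power figure to recompute. The population question is settled by reading. Per protocol excludes patients by adherence; ITT excludes none for that reason. Where any patient departs from the assigned process, the two sets differ.

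**Anchor.** The sections set side by side:

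| Section | 3 months counted from |
|---|---|
| Trial procedures | review |
| Comparison between treatment arms | intervention |
| Measures and measurement instruments | randomisation |

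The first two agree in practice, because the intervention is delivered at the review. The third does not:

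1. The practice is the unit of allocation (Allocation of trial interventions).
2. The invitation letter template states the practice's arm (Patient recruitment), so randomisation comes before patient recruitment.
3. Nurse training differs by arm and is scheduled for January 2013 (Healthcare professional training; Study timeline). If all practices kept to that schedule, allocation was complete by the end of January.
4. Three months from then is the end of April 2013 at the latest.
5. Baseline ran from January to May 2013, before the review (Comparison between treatment arms). For a patient with a May baseline, 3 months after randomisation would fall before both baseline and review.

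**Patients without a review.** A patient can consent, complete baseline, stay in the study and not attend. The planned check covers making the appointment, not keeping it. Counted from the review, that patient has no 3- or 6-month date. The sections shown do not say when such a patient is sent questionnaires, nor that the patient is dropped.

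**Possible size (assumed inputs only).** Let q be the share of an arm left out and d the mAQLQ gap between those left out and those kept in.

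Shift in that arm's mean = q × d

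| q (assumed) | Patients left of 80, if q applies in both arms | Shift, d = 0.5 | Shift, d = 1.0 |
|---|---|---|---|
| 5% | 76 | 0.025 | 0.05 |
| 10% | 72 | 0.05 | 0.10 |
| 20% | 64 | 0.10 | 0.20 |
| 30% | 56 | 0.15 | 0.30 |

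The stated clinically relevant improvement is 0.5, so the range runs from 0.025 / 0.5 = 5% to 0.30 / 0.5 = 60% of it. These are shifts in one arm. The bias in the comparison is the difference between the two arms' shifts, and it is zero if q × d is the same, in size and direction, in both.

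**The case against.** The sentence may be meant as ITT, carried out as the protocol prescribes, and it cites a reference that cannot be seen here. That reading is plausible, but the text does not state it, and a later analysis plan would still have to contradict half of the published sentence. The randomisation anchor looks like a slip: the analysis section gives the same comparison for the same purpose, counted from the intervention. This makes the correction easy but does not remove the conflict. A condensed article may also leave the handling of non-attenders to the full protocol, so that gap carries less weight than the contradictory sentence.

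A reader might infer more than the document supports:

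- **That non-attenders have no outcome and ITT cannot be done.** Trial procedures plans questionnaires for all patients, by post or telephone, so no clinic visit is needed. Baseline mAQLQ is taken before the review. The second withdrawal point concerns patients who leave the study, which is ordinary attrition under any anchor. What is missing is a date for those who stay.
- **That per-protocol exclusions would fall on the intervention arm alone.** The goal tool and its action plan exist only in that arm, so criteria built on them would act on one side and could reveal allocation to a blinded analyst. But no such criteria are given. Review attendance applies to both arms, and patients who forget the tool complete it in the waiting area.
- **That the retention rate is biased.** Retention counts patients followed up and does not depend on the mAQLQ analysis set.

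**Conclusion.** The concern holds in two parts. First, the primary population is contradictory as written, and nothing shown resolves it. This rests on the text alone. Second, the follow-up anchors conflict. Counting from randomisation can place the 3-month point before a patient's review, and counting from the review leaves the date undefined for a patient who remains in the study without attending. The second part puts a complete ITT analysis at risk but does not rule it out.

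No size of bias can be established, because the document gives neither a non-adherence rate nor a score gap; the tabulated range is an illustration. Severity is moderate. Estimating the effect is a secondary aim and no confirmatory conclusion depends on it, but the outcome variability, the ICC and the economic inputs carry forward into the full trial.

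**What to change.** 1. In Statistical analysis, state that the primary analysis is by intention to treat: all consented patients with a baseline questionnaire, analysed in the arm of their practice, whatever review, tool or action plan they received. Make any per-protocol analysis secondary.
2. In Measures and measurement instruments, replace the randomisation anchor with the one used in Trial procedures and Comparison between treatment arms.
3. State that patients without a review are sent the postal or telephone questionnaires at 3 and 6 months from the baseline call.

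The first two are wording changes at no cost. The third costs a few extra questionnaires and slightly mixed timing, since these patients are measured from baseline and the others from the review. It does not settle how a patient who returns no 6-month score enters the regression; that can be left to the analysis plan.

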### Descriptive statistics

#### Describing baseline characteristics of patients and practices

For each study arm, we will describe:

Baseline characteristics of patients: age (mean and SD), gender (number and percentage), quality of life and asthma control.

Baseline characteristics of practices: practice list size (median and IQR, or mean and SD if normally distributed), number of patients on the practice list with an asthma code and the number of patients with active asthma (median and IQR, or mean and SD if normally distributed), age distribution (number and percentage), and deprivation and rurality [proxy measures based on the Information Services Division (ISD) Scotland classification] [45].

#### Comparison between treatment arms

The difference in the validated mAQLQ score between the intervention and control groups at baseline and 3 and 6 months post-intervention will be compared, adjusting for practice level stratum (region and list size). A clinically relevant improvement is an increase of ≥0.5 in individual mAQLQ mean scores [35]. Quality of life using the validated mAQLQ was measured at the baseline (January to May 2013) prior to the HCP asthma review appointment, and repeated at 3 months and 6 months post-intervention. Comparison of the mAQLQ scores at 3 months post-intervention as well as at 6 months post-intervention will enable us to establish the most appropriate time point for assessment of clinical endpoints. Changes from baseline to six months post intervention will be assessed in SPSS for Windows using multiple regression analysis with 6-month mAQLQ as outcome and baseline mAQLQ as covariate along with arm of trial (intervention/control) in the model. We will be adjusting all models for clustering within practices and matching by size. Transformations of the outcome variables will be used where necessary if these are not normally distributed. All analyses will be stratified by the stratification factors. We will estimate an ICC for all potential outcomes in the full trial. Consequently sample size estimates will be made for the full trial.

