#### Patient recruitment

Using the electronic asthma review recall reminder procedures, practices will be asked to identify all eligible patients aged 18 years plus due an asthma review within the proceeding 3-month period. The practice will then write to potential participants informing them that they are due an asthma review and that the practice is participating in the asthma goal project. A template of a covering letter—stating the study arm to which the practice has been allocated—has been provided for this purpose although practices can opt to create/use their own letter. Patients being aware of the study procedure before consenting to take part could lead to a difference in the type of patients participating in the intervention and in the usual care group. Any differences will be identified and controlled for in the final analysis. Accompanying this covering letter will be a project participant information sheet, a consent form and a short screening questionnaire. Interested patients will complete and return the consent form and the screening questionnaire in a pre-paid envelope to the Nursing, Midwifery and Allied Health Professionals research unit (NMHAP-RU) prior to arranging and attending for their asthma review. Patients will be asked to express on the screening questionnaire their preferred day and time to receive a telephone call. All recruitment materials have been approved by East of Scotland Research Ethics Committee (REC 2).

Eligible participating patients will be assigned a unique study identifier and their personal contact details and the original signed consent form scanned and electronically stored in a password-protected folder. One copy of the consent form will be sent to the practice to be inserted into the trial folder along with a letter informing the GP/nurse that the patient had consented to participate in the trial and one copy will be returned to the patient. The original paper copies will be destroyed in accordance with data protection guidelines. A thank-you letter will be sent to all patients who have indicated interest but are not considered eligible to participate informing them that their contact details and consent form will be destroyed safely and in accordance with data protection guidelines.

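### The 6-month mAQLQ comparison is specified both without and with baseline mAQLQ, unranked, and no baseline-adjusted model is written for 3 months

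*Protocol article*

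**What the plan says.** Outcome measures, on the definitive trial: "The main primary outcome measure will be change in quality of life as measured by the mini Asthma-related Quality of Life Questionnaire (mAQLQ"). That sentence gives no time point.

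Comparison between treatment arms describes the mAQLQ analysis twice. First, scores in the two arms "at baseline and 3 and 6 months post-intervention will be compared, adjusting for practice level stratum (region and list size"). Later in the same paragraph, change to six months is to be assessed "using multiple regression analysis with 6-month mAQLQ as outcome and baseline mAQLQ as covariate along with arm of trial (intervention/control) in the model".

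Two further sentences apply throughout: "We will be adjusting all models for clustering within practices and matching by size" and "All analyses will be stratified by the stratification factors". Neither mentions baseline mAQLQ.

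The section also says that comparing scores at 3 and at 6 months "will enable us to establish the most appropriate time point for assessment of clinical endpoints".

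Patient recruitment notes that patients know the study procedure before they consent, which "could lead to a difference in the type of patients participating in the intervention and in the usual care group". It undertakes to control for such differences once identified, but names no variable and no model.

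**The concern.** The two descriptions overlap at 6 months. One has no baseline term and the other does, and nothing ranks them. They give different numbers whenever the arms differ at baseline, so the analyst would have two candidate 6-month effects and no rule for choosing between them.

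At 3 months only the description without baseline exists. The baseline score is the natural covariate, it is taken from patients before the review, and the plan already uses it at 6 months. Leaving it out costs precision. It also leaves the 3-month effect exposed to baseline imbalance, whether by chance with few practices or from the differential recruitment that the protocol itself foresees. The pilot's effect estimates at both times are meant to inform the full trial, so the definition of the effect should be settled before the data are analysed.

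**Working it through.** The article has no figure on this point to reproduce. It states that no formal sample size calculation was done, and its only arithmetic, 8 practices × 10 patients = 80, agrees with the target.

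**Side by side**

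| | First description | Regression |
|---|---|---|
| Times | baseline, 3 and 6 months | 6 months only |
| Baseline mAQLQ | not named | covariate |
| Region and list size | named | through the stratification sentence |
| Clustering and size matching | through the all-models sentence | through the all-models sentence |

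The specifications differ in one thing that matters here, the baseline covariate. They coincide in time only at 6 months.

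**Inputs from the protocol:** 40 patients per arm, 10 per practice, and a clinically relevant individual improvement of 0.5 points.

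**Assumed inputs (not in the protocol):** SD 1.0–1.2 at every visit, ICC 0.02–0.05, correlation r between baseline and follow-up 0.5–0.8.

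**Formulas**
- Design effect: DE = 1 + (10 − 1) × ICC, which is 1.18 at ICC 0.02 and 1.45 at ICC 0.05.
- SE without baseline: SD × √(DE × 2/40).
- SE with baseline: the same × √(1 − r²).
- Gap between the two 6-month estimates: slope × baseline imbalance, where the slope is r if the SDs are equal. Its SD is r × SD × √(DE × 2/40).

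**Results**
- SE without baseline: from 1.0 × √(1.18 × 0.05) = 0.24 to 1.2 × √(1.45 × 0.05) = 0.32.
- SE with baseline: from 0.243 × √(1 − 0.64) = 0.15 to 0.323 × √(1 − 0.25) = 0.28.
- Inflation from omitting baseline: 1/√(1 − r²) − 1, which is 15% at r = 0.5 and 67% at r = 0.8. Simulation gave 14–67%.
- SD of the gap at 6 months: from 0.5 × 0.243 = 0.12 to 0.8 × 0.323 = 0.26.
- Chance that the gap exceeds 0.25 points, half the 0.5-point threshold: about 4% to 33% between those extremes.
- Middle case (SD 1.0, r 0.7, ICC 0.05): SE 0.27 without baseline and 0.19 with it; gap SD 0.19 (95% range ±0.37). A simulation of 8 clusters of 10 gave a gap SD of 0.187 and a gap above 0.25 points in about 17% of trials.
- A baseline imbalance of 0.3 points moves the effect without baseline by 0.3 × 0.5 = 0.15 to 0.3 × 0.8 = 0.24 points.

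Trial status reports ten practices. With ten patients in each, the absolute SEs and gaps shrink by √(80/100) = 0.89, and the ratios do not change.

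**The case against.** The best defence is that the first description covers baseline as well as follow-up. A comparison that includes baseline cannot be baseline-adjusted throughout, so it may be only a by-visit summary. The one regression written out is then the 6-month effect, which fits the change outcome in Outcome measures. This is a reasonable reading, but the text does not state it, and it leaves 3 months with no baseline-adjusted model.

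A reader might infer several stronger claims that the document does not support:

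- *That the first comparison is adjusted for region and list size alone.* The same paragraph adds clustering and size matching to all models. Only the baseline covariate is absent.
- *That the plan will set an unadjusted 3-month effect against a baseline-adjusted 6-month effect.* It does not say so. The time-point sentence refers to scores at both times, which matches the first description, and that uses the same model at each. Baseline imbalance then largely cancels. In simulation under the same assumptions, with equal true effects, the 3- and 6-month estimates differed by more than 0.25 points in 10–44% of pilots with neither adjusted and in 11–45% with both adjusted. The choice of time point is therefore not shown to be distorted.
- *That the 3-month effect is ruled out from ever being baseline-adjusted.* This is inferred from silence. The undertaking in Patient recruitment could bring baseline mAQLQ in, and a fuller analysis plan may list covariates. That undertaking depends on a difference first being found, so it is weaker than a covariate fixed in advance.
- *That a 3-month residual SD will feed the full-trial sample size.* The section mentions an ICC and sample size estimates, but not that input.

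**Conclusion.** The point holds in limited form. The article states two 6-month specifications that differ in baseline adjustment and does not rank them, and it writes no baseline-adjusted model for 3 months.

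The precision loss and the possible disagreement at 6 months are not trivial beside a 0.5-point threshold. Their size rests wholly on the assumed SD, ICC and correlation, and on equal SDs across visits. With a low correlation both are small.

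The consequence is modest. The trial is a feasibility study without a formal sample size, and estimating impact on patient outcomes is a secondary aim. Nothing here undermines recruitment, retention or acceptability, which are its main outputs.

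**What to change.** In Comparison between treatment arms, define the between-arm effect once for both follow-up times: mAQLQ at 3 months, and separately at 6 months, regressed on arm and baseline mAQLQ, with region and list size in the model and allowance for clustering by practice. State that this model supplies the reported effect at each time. Label the baseline comparison, and any follow-up comparison without baseline mAQLQ, as descriptive.

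The cost is a change of wording before analysis, which the Study timeline starts in November 2013. Baseline mAQLQ is already collected, so no new data or patients are needed. The covariate uses one degree of freedom at patient level.
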